## Study design

5

Interventional phase I double-blinded randomized placebo-controlled trial.

## Participants

6

We plan to recruit 100 infertile women undergoing ETs in IVF/ICSI cycles.

## Study setting

7

Patients will be recruited from Melbourne IVF over a period of 12 months. This should allow enough time to achieve adequate participant enrolment to reach target sample size.

## Interventions to be measured

8

This trial will have 2 arms. All capsules will be indistinguishable from each other.(1)Placebo tablet taken once, 30 minutes pre-ET.(2)20 mg immediate release nifedipine tablet taken once, 30 minutes pre-ET

## Primary outcome

9

(1)IR, defined as the presence of serum human chorionic gonadotropic level >5 IU/L following ET.(2)CPR, defined as the presence of a live pregnancy in the uterine cavity at a transvaginal ultrasound at 6 weeks’ gestation onwards.

## Secondary outcome

10

(1)Adverse events defined as any unwanted outcomes, such as dizziness or hypotension, reported in this trial.(2)Miscarriage rate defined as loss of a diagnosed clinical pregnancy before 20 weeks gestation.(3)Pregnancy and neonatal outcomes including multiple pregnancy, congenital or chromosomal abnormalities, stillbirth, preeclampsia, delivery before 34 weeks, delivery between 34 and 37 weeks, necrotising enterocolitis, abnormal neurology, placenta praevia, gestational diabetes, low birth weight, admission to neonatal intensive care unit, duration of admission, need and duration of respiratory support, or any other neonatal morbidity reported.

## Sample size

11

As this is a small scale study, without precedence on which to base accurate power calculations, a power calculation has not been performed. This study should provide guidance for future larger randomized trials. We hypothesis that nifedipine will improve the IR and CPR after IVF/ICSI cycles. A convenient sample of 100 participants, 50 in each arm, was chosen to assess our primary and secondary outcomes.

## Inclusion criteria

12

(1)A total of 18–45 year females undergoing IVF/ICSI cycles and fresh or frozen–thawed ET.(2)Baseline BP greater than or equal to 100/60 mm Hg measured pre-ET.

## Exclusion criteria

13

(1)Body mass index (BMI) greater than 38.(2)Early follicular phase (day 2–4) serum follicle-stimulating hormone level >20 mIU/mL.(3)Abnormal uterine cavity as evidenced by sonohysterogram or hysterosalpingography.(4)Any contraindication to being pregnant and carrying a pregnancy to term.(5)Contraindication for the use of nifedipine, estrogen, and progesterone suppositories.(6)Patient being treated with other drugs that interact with cytochrome P450 activity: azole antifungals, cimetidine, cyclosporine, erythromycin, quinidine, terfenadine, warfarin, benzodiazepines, flecainide, imipramine, propafenone, and theophylline.(7)Irregular heart beat or already being treated with another medication for high blood pressure.(8)Any ovarian or abdominal abnormality that may interfere with adequate transvaginal sonography (TVS) evaluation.(9)Administration of any investigational drugs within 3 months prior to study enrolment.(10)Patient not able to communicate adequately with the investigators and to comply with the requirements of the entire study.(11)Unwillingness to give written informed consent.(12)Previous entry into this study.(13)Baseline BP less than 100/60 mm Hg measured pre-ET.(14)Embryos that have undergone preimplantation genetic screening

## Concomitant care

14

Aside from trial protocol and inclusion criteria listed above, standard concomitant care, such as folic acid supplements, is permitted.

## Participant enrolment

15

This trial will begin recruitment at the level of infertility specialist. Once identified as requiring IVF/ICSI, and satisfying inclusion and criteria, the patient will be provided with detailed written information about the trial protocol. Once informed consent is obtained, then the patient will be randomized to one of the study arms and provided with the trial medication 30 minutes prior to their scheduled ET.

## Allocation concealment, blinding, and randomization

16

Randomization will be performed, by a research assistance, via a computer generated sequence in blocks of 10 recruited subjects. The allocation ratio into each arm will be 1:1. The randomization will be stratified for age into 2 groups: less than 35 years old and greater or equal to 35 years old. Neither patients nor caregivers will be aware of the allocation.

All clinical staff will remain blinded to allocation of therapy until the statistical data base is cleaned and locked. Unblinding only be done in case of urgent medical need.

## Adherence and retention

17

To ensure the integrity of study data, participants adherence to trial protocol, that is, nifedipine administration, will be supervised by the clinical nurse. The time of drug administration, blood pressure pre- and post-ET, and the time of ET will be recorded on the patient record form. Every reasonable effort will be made from the time of enrolment until the end of follow-up to maintain contact with and maintain participant's participation in the trial.

## Analysis plan

18

Primary analysis will occur by the intention-to-treat principle. Statistical comparisons would be carried out using Chi-square test, Fisher exact test, and Student *t* test with the Statistical Program for Social Science (SPSS, Inc., Version 23.0, Chicago, IL). A 2-sided *P* < .05 was taken as statistically significant. Primary and secondary outcomes between placebo group and treatment group would be analyzed using the above statistical comparisons. The baseline demographics of participants, such as age and number of embryo transferred, would also be analyzed to ensure adequate randomization.

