**Methods and analyses::**

We will recruit 100 infertile women into one of 2 groups: placebo (n = 50) and nifedipine 20 mg (n = 50). Study participants will be admitted 30 minutes prior to ET and given either tablet after their baseline vital signs have been recorded. They will then undergo ET and be observed for adverse events for another 30 minutes post-ET. The primary outcome will be implantation rate and clinical pregnancy rate. Secondary outcomes include adverse events, miscarriage and pregnancy, and neonatal outcomes. Resulting data will then be analyzed using *t* test, Chi-square test, and multivariate test to compare outcomes between the 2 groups for any statistical significance. This protocol has been designed in accordance with the SPIRIT 2013 Guidelines.

Key PointsSignificant preliminary research has been performed to form the basis for the design of this trial.This is a randomized, placebo-controlled, double-blind trial to assess nifedipine's effect and safety at the time of embryo transfers.This study has the potential to provide a foundation for future large randomized controlled trialsThis trial is a well-designed randomized controlled trial to assess clinically relevant outcomes.Main limitation of this study is that uterine contractions are not measured and existing variability in embryo quality.

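### Randomisation is stratified by age, but the analysis plan tests outcomes without the strata, and the multivariate test in the abstract has no counterpart there

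*Protocol article*

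**What the plan says.** Protocol article, Section 16 (Allocation concealment, blinding, and randomization): "The randomization will be stratified for age into 2 groups: less than 35 years old and greater or equal to 35 years old". On the ratio: "The allocation ratio into each arm will be 1:1". Blocks are of 10.

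Protocol article, Section 18 (Analysis plan): "Statistical comparisons would be carried out using Chi-square test, Fisher exact test, and Student" *t* test. The section applies these tests to both the primary and the secondary outcomes, with two-sided *P* "< .05 was taken as statistically significant". Age comes up only as a baseline characteristic: "age and number of embryo transferred, would also be analyzed to ensure adequate randomization".

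Protocol article, Abstract (Methods and analyses): the *t* test is listed with "Chi-square test, and multivariate test to compare outcomes between the 2 groups". No multivariable model, covariate or adjusted analysis is described in Section 18 or elsewhere in the body.

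Protocol article, Section 11 (Sample size): "a power calculation has not been performed", and "A convenient sample of 100 participants, 50 in each arm, was chosen to assess our primary and secondary outcomes". No event rate is assumed, overall or by age.

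**The concern.** Stratified allocation balances age between the arms by design. The chance difference between arms therefore no longer contains a part due to age. A test that ignores the strata still counts the age-related variation as error. Its standard error is then larger than the design warrants, so it rejects less often than 5% under the null and less often than it could under an effect.

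With 50 women per arm and no power calculation, there is little power to give away. The article also leaves open which analysis is meant. The abstract points to a multivariate test alongside the simple ones, while Section 18 assigns only simple ones. Two readers could reasonably expect different primary results.

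**Working it through.** **No figure to reproduce.** The article states no power, effect size or event rate. The check therefore asks how the chi-square test behaves under the stated design for a range of assumed rates.

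**Inputs from the article.** Two-sided 0.05 (Section 18); 100 women, 50 per arm (Section 11); 1:1 allocation in blocks of 10, two age strata (Section 16); two binary primary outcomes (Section 9).

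**Assumptions.** Half of the women in each stratum, 25 per arm per stratum; the pregnancy rates in the table below; for power, 20 points added in both strata.

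**Formula.** Let *p*₁ and *p*₂ be the rates in the two strata and *p̄* their mean. Under the null with balance inside strata:

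- The chi-square test uses the pooled variance *p̄*(1 − *p̄*).
- The arm difference actually varies only with the mean of the within-stratum *p*(1 − *p*).
- The excess share is *r* = ¼(*p*₁ − *p*₂)² / [*p̄*(1 − *p̄*)].
- The *z* statistic then has variance 1 − *r*, so the true error is 2 × [1 − Φ(1.96/√(1 − *r*))].

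Numbers put in:

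- 35%/30%: *r* = 0.000625/0.2194 = 0.003; 1.96/√0.997 = 1.963; error 5.0%.
- 45%/25%: *r* = 0.0100/0.2275 = 0.044; 1.96/√0.956 = 2.005; error 4.5%.
- 45%/15%: *r* = 0.0225/0.2100 = 0.107; 1.96/√0.893 = 2.074; error 3.8%.
- 50%/10%: *r* = 0.0400/0.2100 = 0.190; 1.96/√0.810 = 2.178; error 2.9%.

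**Finite-sample check.** Error was simulated with 25 women per arm per stratum. Error and power were also obtained by full enumeration of the 26⁴ possible results, comparing the Pearson chi-square test with the Cochran-Mantel-Haenszel (CMH) test without continuity correction.

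| Assumed rates, <35 / ≥35 | Chi-square error: formula | Simulated | Enumerated | CMH error, enumerated | Power at +20 points, chi-square | Power at +20 points, CMH | Points lost |
|---|---|---|---|---|---|---|---|
| 35% / 30% | 5.0% | 4.9% | 4.9% | 4.9% | 54.4% | 54.4% | 0 |
| 45% / 25% | 4.5% | 4.5% | 4.4% | 4.9% | 54.4% | 54.7% | 0.3 |
| 45% / 15% | 3.8% | 3.7% | 3.8% | 5.0% | 54.7% | 57.6% | 2.9 |
| 50% / 10% | 2.9% | 3.0% | 2.9% | 5.1% | 54.8% | 61.9% | 7.1 |

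The three routes to the chi-square error agree to about 0.1 point.

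**Blocks of 10.** A last block that is not filled leaves some imbalance within a stratum, so the real design is slightly less conservative than exact balance. Simulation with permuted blocks of 10 in each stratum gave chi-square errors of about 4.7% at 45%/25%, 3.8% at 45%/15% and 3.1% at 50%/10%. The stratified test held 5.0% to 5.1%.

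**Comparison of the passages.** Section 16 makes age a design factor. Section 18 names the outcome tests and uses age only to describe baseline. The abstract names a further multivariate test for comparing outcomes between the arms. The abstract and Section 18 cannot both be a full statement of the outcome analysis.

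**The case against.** The strongest reply is that the harm is small and on the safe side. Ignoring the strata does not raise the false-positive rate and does not bias the arm difference. The article calls the trial phase I, uses a convenience sample and looks ahead to larger trials. A loss of 3 to 7 power points needs a gap of 30 to 40 points between the age groups, and nothing in the article supports or excludes such a gap. All of this stands, and it limits the weight of the point.

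A second reply is that an unseen analysis plan may define the multivariate model and handle age there. That may be so, and the missing model details are not counted as an error here. But Section 18 does assign specific unstratified tests to the primary and secondary outcomes, and it differs from the abstract. The mismatch is in the text at hand.

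Four stronger readings may tempt a reader, and the article does not support them:

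- *The primary test certainly runs below 5%.* It does so only if age is prognostic. The article gives no reason for stratifying and no rates by age, and at 35%/30% the effect is negligible.
- *Naming both chi-square and Fisher leaves the primary test to choice.* The list covers all outcomes together, including rare neonatal events where an exact test is usual. When to use which is a detail that a condensed article may leave out. Fisher's conservatism also comes mainly from its discreteness, not from ignoring age.
- *Baseline comparisons will drive the choice of covariates.* Section 18 says that baseline data will be analysed, but it describes no selection of covariates from them.
- *Any form of age adjustment brings free precision.* That holds for a stratified test or risk difference. Logistic adjustment gains power but does not shrink the standard error of the log odds ratio, and it changes the quantity estimated.

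**Conclusion.** The point holds as a consistency and efficiency issue that should be corrected. It does not threaten validity. The mismatch between Sections 16 and 18, and between the abstract and Section 18, is certain from the text. Its statistical cost depends on how strongly age predicts pregnancy in this population:

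- a gap of 5 points between the age groups costs nothing visible;
- a gap of 20 points puts the true error near 4.5% and costs about 0.3 power points;
- gaps of 30 and 40 points put the error near 3.7% and 3.0% and cost about 3 and 7 power points.

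These figures rest on assumed rates, equal strata, balance within strata and a common 20-point effect. Under the same assumptions the age-stratified test stays near 5%.

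**What to change.** In Section 18, make the primary analysis of each binary primary outcome age-stratified: a CMH test over the two randomisation strata, reported with the Mantel-Haenszel risk difference and its 95% confidence interval. The risk difference is the weighted mean of the two stratum differences, with weight *n*₁*n*₀/(*n*₁ + *n*₀) in each stratum, where *n*₁ and *n*₀ are the numbers in the two arms. For continuous outcomes, replace the plain *t* test with a comparison adjusted for age stratum.

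Then align the abstract with Section 18 on this one analysis: either remove the multivariate test from the abstract, or define it in Section 18 with its model, covariates and role.

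The cost is analysis-plan wording only. Sample size, randomisation and data collection are unchanged.

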## Discussion

23

Implantation failure is a major factor limiting the success of IVF/ICSI treatment and excessive UCs is one of the mechanisms contributing to implantation failure. Given nifedipine's tocolytic properties, safety profile, and use in obstetrics practice, it is a promising candidate to improve the outcomes of IVF/ICSI treatment. This trial is essential to confirm the efficacy, side effects, and safety of nifedipine in infertility treatment. If this study confirms that nifedipine favors a positive outcome, we will then proceed to a phase II randomized controlled trial. A phase I trial to investigate the clinical benefits, namely improved implantation and pregnancy rate of nifedipine in IVF/ICSI treatment cycle, has been initiated.

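### The Discussion promises to confirm nifedipine's safety, but difference tests at P < .05 in an unpowered 50 per arm cannot confirm the absence of uncommon or pregnancy-dependent harms

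*Protocol article*

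**What the plan says.** Four places in the protocol article bear on this.

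- **Discussion (section 23).** The purpose is stated as confirmation: "This trial is essential to confirm the efficacy, side effects, and safety of nifedipine in infertility treatment".
- **Secondary outcome (section 10).** The outcomes are adverse events, miscarriage before 20 weeks, and a list of pregnancy and neonatal complications. The first is broad: "Adverse events defined as any unwanted outcomes, such as dizziness or hypotension, reported in this trial". Miscarriage is defined as loss of a diagnosed clinical pregnancy, so only women with a clinical pregnancy can contribute an event.
- **Analysis plan (section 18).** "Statistical comparisons would be carried out using Chi-square test, Fisher exact test, and Student *t* test"; "A 2-sided *P* < .05 was taken as statistically significant"; and then "Primary and secondary outcomes between placebo group and treatment group would be analyzed using the above statistical comparisons". The Abstract also mentions a multivariate test, again aimed at statistical significance.
- **Sample size (section 11).** "a power calculation has not been performed", and "A convenient sample of 100 participants, 50 in each arm, was chosen to assess our primary and secondary outcomes". The same section calls the study small and a guide for larger trials.

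The article gives no expected event rate, no expected number of pregnancies and no size of excess harm to be ruled out.

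**The concern.** A test of no difference is asymmetric. A small P-value is evidence of harm. A large one shows only that the data were not extreme enough to reject equality, and in a small sample that is the likely result whether or not the drug does harm. The stated aim (confirm safety) and the stated method (test for a difference, in a sample not sized for one) therefore do not fit together.

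The misfit matters most for uncommon events and for events that need a pregnancy, where the effective denominator is well below 50 per arm. For these, a non-significant comparison is the expected finding even under a material increase, and the data would still be compatible with a large excess. A report that honoured both sections as written could claim more about safety than its data support.

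**Working it through.** **Inputs from the protocol article.** Two-sided alpha 0.05, with Chi-square and Fisher exact tests (Analysis plan). 50 women per arm (Sample size). "The allocation ratio into each arm will be 1:1" (Allocation concealment, blinding, and randomization).

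**Inputs assumed, because the article gives none.** Event rates in each arm, and 12 to 20 clinical pregnancies per arm.

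**The plan's own figure.** There is none to reproduce: no power, effect size or margin is stated.

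**Power.** For n per arm and true rates p0 (placebo) and p1 (nifedipine), exact power is the sum, over all pairs (x, y) for which the test gives P < .05, of Bin(x; n, p0) × Bin(y; n, p1). Results:

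| n per arm | p0 vs p1 | Fisher | Uncorrected chi-square |
|---|---|---|---|
| 50 | 5% vs 10% | 0.06 | 0.15 |
| 50 | 5% vs 15% | 0.24 | 0.39 |
| 50 | 10% vs 20% | 0.20 | 0.30 |
| 50 | 10% vs 30% | 0.64 | 0.73 |
| 50 | 20% vs 40% | 0.52 | 0.60 |
| 12 to 20 | 15% vs 30% | 0.05 to 0.12 | 0.12 to 0.21 |
| 12 to 20 | 20% vs 40% | 0.09 to 0.19 | 0.18 to 0.29 |
| 20 | 10% vs 30% | 0.24 | 0.36 |

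The chance of missing the harm is one minus the entry. For example, 5% vs 15% at 50 per arm is missed 1 − 0.24 = 76% of the time with Fisher and 1 − 0.39 = 61% with chi-square.

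**Where the problem stops.** At 50 per arm, power is below one half for a doubling when the placebo rate is up to about 15–18%, and for a tripling when it is up to about 6–8%. Above those rates, harm of that relative size would more often than not reach significance.

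**What a non-significant result would leave open.**

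- Suppose 5/50 on placebo and 12/50 on nifedipine. The risk difference is 24% − 10% = 14 points and Fisher P = 0.108. The Wilson 95% limits are 4.3% to 21.4% for 5/50 and 14.3% to 37.4% for 12/50. The Newcombe limits are then
  - lower: 14 − √[(24.0 − 14.3)² + (21.4 − 10.0)²] = −0.9 points;
  - upper: 14 + √[(37.4 − 24.0)² + (10.0 − 4.3)²] = 28.6 points.

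  The comparison is non-significant, yet an excess of more than a quarter of women is not excluded.
- With no events on placebo, 6/50 on nifedipine are needed for Fisher P < .05 (0 vs 6 gives P = 0.027).
- With no congenital anomaly in 15 pregnancies, the one-sided 95% upper limit is 1 − 0.05^(1/15) = 18.1%.

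**The case against.** The strongest reply has four parts.

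1. **No rule equates P > .05 with safety.** This is correct. A reader might infer from the Discussion that a null comparison will be read as safe and carried into the next phase. The article says neither: its only stated condition for a phase II trial is that the study favours a positive outcome. The point therefore rests on the mismatch between aim and method, and attributes no decision rule to the investigators.

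2. **Confidence intervals may sit in a full protocol or analysis plan that is not shown.** This also stands, and their absence from an article is not the finding. What the article does fix is a claim of confirmation together with difference testing of the harm outcomes in an unpowered sample. Intervals reported elsewhere would help interpretation but would not make the word confirm accurate.

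3. **A doubling or tripling of harm is not always missed.** A reader might generalise from the low-power cases, but the table contradicts that for commoner events. The Introduction lists flushing, headache, nausea, tachycardia and hypotension as the most common side effects, so rates high enough for reasonable power are possible. The point is limited to uncommon and pregnancy-dependent harms.

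4. **Safety is handled elsewhere, and the study admits that it is small.** The adverse events section has blood pressure and heart rate measured before and after transfer, and serious adverse events recorded separately, followed up and reported. That is useful surveillance, but it is not a comparison between arms. The disclosure in the Sample size section is candid, and it is a further reason not to promise confirmation in the Discussion.

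**Conclusion.** The point holds in a limited form. The article promises to confirm safety, but the only between-arm method it fixes for harms is a test of difference at two-sided P < .05, with 50 per arm and no power calculation. That method can flag harm and cannot confirm its absence. For uncommon harms (around 5% on placebo), exact power against a doubling or tripling is between 0.06 and 0.39 at 50 per arm. For a doubling of miscarriage from 15%, it is between 0.05 and 0.21 with 12 to 20 pregnancies per arm. All rates and pregnancy counts are assumptions, and at higher base rates detection is more likely than not. The tests themselves are not wrong. What they cannot carry is the conclusion placed on them.

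**What to change.** - **Analysis plan (section 18).** For adverse events, miscarriage, and the main pregnancy and neonatal outcomes, make the comparison one of estimation: counts per arm with their denominators, and the risk difference with its 95% confidence interval (Newcombe or exact would suit these counts). Base any safety statement on the upper limit. State that a non-significant result will not be taken as evidence of safety. P-values may still be shown as a signal of harm.
- **Discussion (section 23).** Replace the promise to confirm safety with wording such as: describe side effects and estimate, with confidence limits, any excess harm.

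The cost is a few sentences and routine output, with no extra patients or data. The downside is a more modest safety claim, which fits the role that the Sample size section already gives this study as a guide for larger trials.

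### Baseline comparisons cannot show that randomisation was adequate; at 50 per arm they would pass sizeable chance imbalances, and section 18 gives IR and CPR only unadjusted tests

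*Protocol article*

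**What the plan says.** Section 18 (Analysis plan) of the protocol article gives the baseline analysis a purpose: "The baseline demographics of participants, such as age and number of embryo transferred, would also be analyzed to ensure adequate randomization". The methods in that section are these: "Statistical comparisons would be carried out using Chi-square test, Fisher exact test, and Student" *t* test, at a two-sided 5% level. The section then assigns the same comparisons to the primary and secondary outcomes. It names no adjusted analysis and no covariate.

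The abstract (Methods and analyses) differs: besides the t and chi-square tests it lists a multivariate test for comparing outcomes between the groups, without covariates.

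Section 16 covers allocation: "The allocation ratio into each arm will be 1:1", in blocks of 10, and "The randomization will be stratified for age into 2 groups: less than 35 years old and greater or equal to 35 years old". Age is the only stratification factor. Number of embryos transferred, the other variable named for the baseline check, is not stratified.

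On size, section 11 says: "A convenient sample of 100 participants, 50 in each arm, was chosen to assess our primary and secondary outcomes", and that "a power calculation has not been performed". The key points concede unexplained prognostic variation: "Main limitation of this study is that uterine contractions are not measured and existing variability in embryo quality".

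**The concern.** Adequate randomisation is secured by how the sequence is generated, concealed and followed. If that is done properly, the null hypothesis of every baseline test is true by design. A small P value is then a chance event, and a large one does not mean the arms are alike. What matters for the result is the size of an imbalance multiplied by the prognostic strength of the variable, and the baseline P value does not measure that product.

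With 50 women per arm the tests are also weak. A chance imbalance in a predictor of pregnancy could pass as adequate and carry straight into an unadjusted comparison of implantation rate (IR) or clinical pregnancy rate (CPR). In the other direction, a chance P < .05 could be read as failed randomisation in a sound trial. The Discussion makes a favourable result the trigger for a phase II trial, so a tilt in the observed difference bears on a real decision.

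**Working it through.** **Inputs from the protocol article.** 50 women per arm (section 11), 1:1 allocation stratified by age at 35 (section 16), and two-sided 0.05 with chi-square, Fisher and t tests (section 18). The article states no power, event rate or effect size, so there is no figure of its own to reproduce.

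**Assumed inputs.** The prognostic strength of the baseline variables and the pregnancy rate. The article gives neither, so ranges are shown.

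**1. Continuous variable: what passes.** The smallest significant observed standardised difference is t(0.975, 98) × √(2/50) = 1.984 × 0.2 = 0.397. Observed differences up to about 0.39 SD are non-significant. Power of the baseline t test at a true difference of 0.5 SD is 0.697, so it misses such a difference 30% of the time.

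**2. Binary variable: what passes.** Largest non-significant count in the second arm, by enumeration:

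| First arm | Chi-square (uncorrected) | Fisher |
|---|---|---|
| 10/50 | 18/50 (16 points) | 19/50 (18 points) |
| 15/50 | 24/50 (18 points) | 25/50 (20 points) |
| 20/50 | 29/50 (18 points) | 30/50 (20 points) |
| 25/50 | 34/50 (18 points) | 35/50 (20 points) |

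For 15/50 versus 24/50, the pooled proportion is 39/100 = 0.39, SE = √(0.39 × 0.61 × 2/50) = 0.0975 and z = 0.18/0.0975 = 1.85. Chi-square P = 0.065; Fisher P = 0.100. With 39 two-embryo women split by simple 1:1 allocation, an imbalance this large in either direction occurs about 10% of the time.

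**3. Effect on the arm difference.** Shift = difference in prevalence × effect of the factor on the pregnancy rate. For two-embryo transfer at 30% versus 48%:

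- effect of 10 points (assumed): 0.18 × 10 = 1.8 points
- effect of 15 points: 0.18 × 15 = 2.7 points
- effect of 20 points: 0.18 × 20 = 3.6 points

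Over a wider assumed range of 5 to 30 points, an 18- to 20-point imbalance gives 0.18 × 5 = 0.9 up to 0.20 × 30 = 6 points. For a continuous variable, shift ≈ p(1 − p) × ln(OR per SD) × 0.396. This gives 2.2 points at p = 0.30 and OR 1.3, and 6.6 points at p = 0.40 and OR 2.0.

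**4. Effect on the error rate, given that imbalance.** In a simulation with no drug effect, a 25% base rate and a 15-point second-embryo effect (both assumed), with 15 versus 24 two-embryo women, the false-positive rate is 4.5% in the favoured direction and 1.1% in the other. The total is 4.5 + 1.1 = 5.6%. By normal approximation at a 30% or 40% event rate, total error is about 5.5% for a 2-point shift, 7% for 4 points and 9 to 10% for 6 points.

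**5. Abstract and section 18 side by side.** The abstract announces a multivariate comparison of outcomes. Section 18, the operative text, gives the outcomes only unadjusted tests. The two do not describe the same primary analysis.

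**The case against.** Several points on the other side have force.

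- **No decision rule.** A reader might infer that the plan takes a non-significant baseline difference as proof of comparability. The text does not say so. It sets no action after either result, and it assigns the tests explicitly only to the outcomes. This stands as a limit on wording. The stated purpose, next to a list that contains only significance tests, still makes that the natural reading.
- **Adjustment is announced.** A reader might infer that embryo number never enters an outcome analysis. The abstract's multivariate test rules out so flat a statement. A missing covariate list alone is no fault in a condensed article, but the mismatch with section 18 is on the page.
- **Small, conditional effect.** A reader might infer that the primary test is biased. Over repeated randomisations it is not: it keeps its 5% level. The worked imbalance is one that chance produces about 10% of the time or less, and total error in that example is 5.6%. The prognostic strength is assumed. All of this stands.
- **Age is partly protected.** Stratifying at 35 limits gross age imbalance, so the concern applies mainly to embryo number.
- **False alarms.** Ten independent tests would give at least one P < .05 with probability 1 − 0.95^10 = 40%, but ten is an assumption. The article names two variables as examples, for which the figure is 1 − 0.95² = 9.75%.
- **A legitimate use.** A baseline test can point to faulty allocation, so it is not wholly uninformative. Even so, it cannot ensure that allocation was sound.

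**Conclusion.** The point holds in a limited form. The stated purpose of the baseline analysis is unsound: the tests named cannot ensure randomisation, and at 50 per arm they pass observed differences of about 0.39 SD, or 16 to 18 percentage points by chi-square. An imbalance of that size in embryo number would shift the observed arm difference by 1.8 to 3.6 points if a second embryo is worth 10 to 20 points. That rests on an assumed effect and on the imbalance having occurred. It does not make the unadjusted test invalid over repeated randomisations, and the documents do not support a claim that the plan formally certifies comparability by P value. Separately, the abstract and section 18 disagree on whether outcomes receive an adjusted analysis. Both are worth correcting because the repair is nearly free.

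**What to change.** 1. In section 18, delete the clause that gives checking randomisation as the purpose of the baseline analysis, together with any baseline significance tests. Report baseline data descriptively by arm.
2. Reconcile the abstract with section 18. State in both that the IR and CPR comparisons are adjusted for the age stratum (<35 versus ≥35, the randomisation factor) and the number of embryos transferred (one versus more than one), whatever imbalance is observed. Embryo number qualifies only if it is fixed before dosing. The article does not say when it is decided, so this should be confirmed and stated.
3. Report the adjusted risk difference with its 95% CI alongside the unadjusted result.

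The cost is a few sentences and slightly more modelling work than a 2×2 test in a 100-woman trial. Both covariates are already among the baseline data the plan intends to analyse.
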